#### Moderator and mediator analyses

Moderator analysis will be performed by including the moderator variable as an additional fixed factor or covariate in the regression models, and examining interaction effects. The following moderator analyses are planned: (a) educational level (completed high school), (b) readiness to change, (c) baseline AUDIT score (8–12 versus > = 13), (d) tobacco use (yes/no), (e) illicit drug use (yes/no) and (f) HrQoL subgroups based on the EQ-5D scale. Participants who are less ready to change [66] and with more severe problems [67] (as reflected in higher baseline AUDIT scores, co-occurring tobacco use and illicit drug use and lower QoL) could respond differently to the counselling programme compared to participants who are ready to change and have less severe problems, respectively. We will also use multi-level structural equation modelling to test a multi-mediation model that assesses whether problem-solving skills, self-efficacy and social support mediate the effect of the intervention on outcomes and the extent to which individual variables mediate the effect conditional on the presence of other mediators in the model.

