##### Health-related quality of life (HrQoL)

The EuroQol 5 (EQ-5D) will assess HrQoL. The EQ-5D generates a single index that measures how much someone’s life could be extended and improved [53]. From this index, quality-adjusted life years (QALY) will be estimated.

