#### Possible mediators and moderators of outcomes

We will collect information on a variety of variables thought to potentially mediate or moderate response to the counselling intervention. The 25-item Social Problem-Solving Inventory Revised-Short Form will be used to assess problem-solving styles. This has been adapted for use among South African populations [54]. The MOS Social Support survey will assess nature and extent of social support [55]. We will also use the 10-item Generalized Self-efficacy Scale to assess participants’ confidence in their ability to solve and cope with a range of problems [56] and the Trauma History Questionnaire will examine lifetime trauma exposure [57]. We will assess other risk behaviours that may impact on study outcomes. We will examine frequency, quantity and chronicity of tobacco use. In addition, the 11-item Drug Use Disorders Identification Test will assess harmful patterns of illicit drug use and dependence [58]. The 10-item Kessler psychological distress scale will examine extent of psychological distress [59].

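### Moderation by severity is tested with baseline AUDIT cut in two and the EQ-5D in subgroups, although both full scores are collected; a median cut would lose about 36% of the interaction information

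*Protocol article*

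**What the plan says.** All references are to the protocol article. Under Moderator and mediator analyses, moderators will be tested by "including the moderator variable as an additional fixed factor or covariate in the regression models, and examining interaction effects". The list includes "c) baseline AUDIT score (8–12 versus > = 13", and then "d) tobacco use (yes/no), (e) illicit drug use (yes/no) and (f) HrQoL subgroups based on the EQ-5D scale". Readiness to change is also listed, without a cut.

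The reason given is that people with more severe problems may respond differently, with severity "as reflected in higher baseline AUDIT scores, co-occurring tobacco use and illicit drug use and lower QoL".

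On what is collected:
- The AUDIT is a primary outcome measured at baseline and at both follow-ups (Primary outcome measures).
- "The EQ-5D generates a single index" (Health-related quality of life).
- For drugs, "the 11-item Drug Use Disorders Identification Test will assess harmful patterns of illicit drug use and dependence"; for tobacco, "We will examine frequency, quantity and chronicity of tobacco use" (Possible mediators and moderators of outcomes).

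Under Trial objectives, moderators are something to explore within the secondary objectives. Sample size considerations gives power for main effects only.

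**The concern.** For AUDIT and quality of life the hypothesis is about degree: the higher the score, or the lower the quality of life, the more the response may differ. A two-band AUDIT factor treats a score of 13 the same as a very high score and separates 12 from 13. EQ-5D subgroups likewise ignore all variation within each group. The protocol gives no reason for either choice, and its own model wording already allows a moderator to enter as a covariate.

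Interaction tests generally have less power than main-effect tests, and this trial was sized for main effects. Coarse moderators weaken them further, so real modification by severity is more likely to be missed and reported as absent.

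**Working it through.** **1. The plan's own figures.** These are main-effect figures, and they reproduce. Inputs from Sample size considerations: two-sided α 0.05, power 90%, ICC 0.030, 20 per cluster; AUDIT difference 3, SD 6.5; CES-D difference 5, SD 10.
- Design effect: 1 + (20 − 1) × 0.03 = 1.57.
- AUDIT: 2 × (1.960 + 1.282)² × 6.5² / 3² gives 99 per arm; 99 × 1.57 / 20 = 7.77, so 8 clinics, as stated.
- CES-D: the same formula gives 85 per arm; 85 × 1.57 / 20 = 6.67, so 7 clinics, as stated.

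No power, expected size or sample size is stated for any interaction, so the rest needs assumptions.

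**2. Information kept after a cut.** Assume a normal score and moderation linear in it. With share p above the cut, the fraction of interaction information kept is φ(z_p)² / [p(1 − p)].
- 50:50: 0.3989² / 0.25 = 0.637.
- 20:80: 0.2800² / 0.16 = 0.490.

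**3. Power after a cut.** Power = Φ[(1.960 + z_power) × √kept − 1.960], where the first bracket is 2.802 for a starting power of 80% and 3.242 for 90%. For a median split from 80%: 2.802 × 0.798 − 1.960 = 0.276, which gives 61%.

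| Grouping | Information lost | From 80% | From 90% |
|---|---|---|---|
| Two groups, 50:50 | 36% | 61% (−19) | 73% (−17) |
| Two groups, 30:70 | 42% | 57% (−23) | 69% (−21) |
| Two groups, 20:80 | 51% | 50% (−30) | 62% (−28) |
| Three equal groups, scored | 21% | 70% (−10) | 82% (−8) |
| Four equal groups, scored | 14% | 74% (−6) | 85% (−5) |

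**4. The AUDIT cut specifically.** Among scores of 8 or more, the AUDIT is truncated and not normal. The squared correlation between the cut at 13 and the full score was simulated under seven assumed shapes (truncated exponential and truncated normal). It ranged from 0.61 to 0.38, a loss of 39% to 62%.

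**5. Dependence on interaction size.** Take completers per arm as 8 × 20 = 160 (one disease) or 320 (both), remove the 3% ICC from the variance, and suppose the treatment effect differs between the two halves of a median split by half the planned main effect. The slope per moderator SD is that difference divided by 2 × 0.798, and the standard error is SD × √0.97 × √(2/n).
- AUDIT, 1.5 units, n = 160: slope 0.940, standard error 0.716; power 26% with the full score, 18% with the split. With n = 320: 46% and 32%.
- CES-D, 2.5 units: 30% and 21% with n = 160; 52% and 36% with n = 320.

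The cost here is 8 to 16 points. If the difference equals the full planned effect, it is 9 to 19 points (for example AUDIT with n = 160: 75% and 55%). If half the planned effect is instead taken per moderator SD, with n = 320 and no ICC adjustment, AUDIT power is 83% with the full score, 64% at 50:50 and 53% at 20:80; CES-D power is 88%, 71% and 60%. The proportion of information lost is the same under each convention; only the starting power moves.

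**The case against.** The best reply has four parts.

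- **Tobacco and drugs.** A reader might infer that all the yes/no moderators contradict a graded hypothesis. They do not. For these two, the stated marker of severity is co-occurring use, which is presence, so a yes/no factor tests what is written. The protocol names no tobacco score, and drug and tobacco scores may contain many zeros, which makes user versus non-user a natural contrast. This part stands in full.
- **EQ-5D.** The number of subgroups and their limits are not given, and an article may leave them to the analysis plan. That stands: their absence is no fault, and two-group losses cannot simply be applied. The choice of subgroups over the index is, however, made in the protocol.
- **Size.** A reader might quote a third to a half of the information and 15 to 20 points of power as facts of this trial. The documents do not support that. Losing half the information costs 28–30 points from 80–90% power, and 15–20 points fits only cuts near the median. Every power figure also rests on an assumed score shape, split and interaction size. This part stands.
- **Status.** Moderation is exploratory and no interaction power is claimed, so nothing stated is false, and these tests should not be treated as confirmatory. This also stands.

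None of this favours cutting the AUDIT score, or using subgroups for the main EQ-5D test.

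**Conclusion.** The point holds for baseline AUDIT, where the two-way cut is explicit, and for the EQ-5D, where subgroups replace an available index. In both, the coding is coarser than the rationale and the data. Under linear moderation in a roughly normal score, the loss is about 36% of interaction information at a median split and 51% at 20:80, but only 21% or 14% with three or four equal groups. The power cost is conditional: 17–19 points (median) or 28–30 (20:80) from a starting power of 80–90%, and 8–16 points at a median split if the interaction is small, where either test is weak. If moderation is really a step at the cut, the bands lose nothing. It does not extend to tobacco and drug use as yes/no. Severity is minor.

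**What to change.** Under Moderator and mediator analyses, define the main exploratory moderator tests as treatment arm by continuous baseline AUDIT score and treatment arm by continuous baseline EQ-5D index, each with one non-linear term as a check. Keep the AUDIT bands and EQ-5D subgroups only to display estimated effects at low and high severity. State which participants the AUDIT test covers, since the bands begin at 8 while a patient may enter on the depression screen alone.

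Leave tobacco and illicit drug use as yes/no. The 11-item drug-use score could be added alongside the user indicator as a supplementary graded test.

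The cost is a wording change before analysis, with no new data. The downside is that the main test assumes an approximately linear trend, which the non-linear term checks, and a slope is slightly less simple to present than two subgroup effects.

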### Ethical considerations

The South African Medical Research Council (EC 004–2/2015), the University of Cape Town (089/2015), and Oxford University (OxTREC 2–17) provided ethical approval for this study. The Western Cape Department of Health also approved this study (WC2016_RP6_9). The trial is registered with the Pan African Clinical Trials Registry (PACTR201610001825403). Informed consent will be obtained from all potential individual participants prior to enrolment. Prospective participants will be informed of all foreseeable risks of study involvement, that participation is voluntary and will not affect their clinical care, and that they may withdraw their consent without this affecting their medical care. The consent forms are available in English, Afrikaans and isiXhosa, the main languages spoken in the region.

To ensure confidentiality, a unique participant identification number will link the various study forms. We will collect data using an electronic data collection platform that will transmit data in real time to a central database, enhancing data safety. The study database will be password-protected following standard password safety procedures. The data manager will review these data daily for quality assurance and quality control purposes. All data not stored electronically will be stored in double-locked filing cabinets in designated locked offices. Forms with personal identifying information will be stored separately from case report forms. Study records will not be available to participants’ health care providers. We will however ask participants’ consent to share their HbA1c and HIV RNA viral load test results with their providers as these results may improve the clinical care they receive.

The main risk associated with this study, shared with other psychotherapy interventions, is initial worsening of symptoms and risk of suicide arising from issues uncovered during counselling [68]. To minimize this potential harm, we will train staff to screen all participants who report or display signs of distress for risk of suicide (using the Columbia Suicide Severity rating scale [69]) and to provide referrals (based on severity of risk) to specialised mental health services. There are also potential benefits to participation. All participants will benefit from screening for CMDs and referral to mental health care as appropriate. All participants will obtain more regular chronic disease monitoring (biannual versus annual) which may lead to better disease management. We anticipate that participants in the intervention arms will improve their mental health, adhere better to chronic disease care and reduce their risk of chronic disease treatment failure. Finally, on completion of the trial, all participating clinics (regardless of allocation) will be trained in the integrated approach found to be most effective, thus creating opportunities for improved clinical care for patients with chronic diseases.

### Trial management

A trial steering committee will be convened to provide overall supervision of the trial, ensure its conduct is in accordance with the principles of relevant regulations, and monitor data and trial safety. Within the trial steering committee, a smaller data safety monitoring board will monitor adverse and serious adverse events related and unrelated to the trial. In addition, we will create a stakeholder advisory group (SAG) comprising representatives from the WCDOH, health care providers, CHWs, non-governmental organisations and mental health and chronic disease service users. The SAG functions to ensure the trial is responsive to the needs of the health system, its partners and service constituency and to consider how findings from the trial can guide the implementation of mental health counselling in PHC facilities.

## Discussion

In recent years, there have been several global mental health initiatives to identify and strengthen the core elements of health systems required for integrating mental health counselling into PHC services [21, 25] and on implementing task-shifted mental health interventions into primary care services [33]. Some of these initiatives have advocated for additional staffing resources to enable the delivery of integrated care, while others have used staffing resources already present in the system to deliver these additional services. Yet, uncertainty about which of these approaches to service integration is the most effective and cost-effective has hampered the scale-up of mental health counselling [25, 33]. The proposed study will respond to this question by comparing the relative benefits of these two common approaches to mental health service integration on both mental and physical health outcomes. These findings will advance scientific knowledge in the field of mental health service implementation by identifying a model of mental health service integration that is effective and cost-effective.

This study has several strengths. The inclusion of chronic disease biomarkers and patient-level economic cost data is novel and allows for the objective demonstration of the benefits of treating CMDs for chronic disease outcomes as well as potential productivity gains. Another strength is the generalizability of findings and thus potential for high impact. First, we will be recruiting participants across multiple HIV and diabetes clinics in the Western Cape. As we are working across multiple clusters located in both rural and urban communities, findings are likely to be generalizable to other HIV and diabetes services in the province. Second, chronic disease services in the Western Cape are similar to chronic disease services in other parts of South Africa: they are busy, under-resourced, and a significant proportion of patients have co-occurring mental disorders [25]. Third, this study examines mental health counselling integration in a chronic communicable and NCD service provided by vertically distinct services co-located within PHC clinics. Should either approach to service integration prove more effective and cost- effective for both HIV and diabetes service settings, we would have identified an approach to mental health service integration with potential applicability across a range of chronic disease services. The likelihood of this study influencing health services is good as senior officials from the WCDOH are part of the investigative team and SAG, enhancing the likelihood that findings from this study will be able to influence the roll out of integrated mental health care services [70]. Further, as the generalizability of outcomes to more than one type of chronic disease and more than one region may influence the implementation of integrated mental health care, findings from this study have the potential to strengthen and expand access to mental health treatment for chronic disease patients.

Fourth, findings from this study may be generalizable to other similar LMICs. South Africa and other LMICs are experiencing an epidemiological transition from a disease burden dominated by communicable diseases to one characterised by both chronic communicable and NCDs [71]. As South Africa faces a quadruple burden of communicable diseases, NCDs, injury and mental disorders [1], it provides an ideal laboratory for health system interventions that are potentially useful for other LMICs experiencing similar epidemiological transitions. With this epidemiological transition in mind, the Sustainable Development Goals initiative has challenged countries to achieve a 30% reduction in premature deaths due to NCDs by 2030 [72]. In order to achieve this goal of improving NCD treatment outcomes, the delivery of NCD services within LMICs requires strengthening. Similar to other LMICs, South Africa’s PHC system has focused primarily on responding to the burden associated with communicable diseases, with NCD services being less resourced and developed [73]. As project MIND will generate information on the relationship between mental health counselling, treatment adherence, and clinical outcomes of NCD treatment outcomes, it has the potential to guide efforts to strengthen NCD services both locally and in other LMICs.

Despite these strengths, we anticipate some challenges to trial implementation. Recruitment of individual participants may pose challenges given the reliance on facility staff for the initial identification of suitable patients to approach for screening. To address this potential challenge to recruitment, we have developed a PHC facility engagement strategy that includes regular meetings with facility management, implementation readiness workshops to build a shared commitment to the study, joint trouble-shooting of challenges, and regular feedback of study progress at facility meetings. Second, retention of participants in a three-session intervention and through the lifespan of the study may pose some challenges. We have a comprehensive strategy to limit attrition (including reimbursement of transport costs) that has been used in other studies where we have obtained more than 80% follow-up rates [74]. Third, there are other ongoing initiatives to integrate and strengthen PHC services in the province; these other initiatives and contextual differences between facilities may affect study findings. We will collect contextual information and information on other service improvement initiatives regularly from each clinic in order to account for any additional bias. Another potential challenge relates to the quality of counselling provided by CHWs given that CHWs may have low levels of mental health literacy. Although the quality of counselling has a significant influence on the proposed outcome, in order to enhance the quality of care in both of the intervention arms, we plan to monitor the quality and idelity of counselling closely. We also plan to interview participants about their experiences of counselling. Through monitoring and participant feedback, we will learn about the amount of training and supervision needed to develop mental health care competencies among CHWs. This information is likely to be relevant for the implementation of other health programmes involving CHWs.

In summary, this study has the potential to fill an important knowledge gap regarding effective and cost-effective approaches to integrating mental health counselling into chronic disease care. Evidence generated by this study will be of direct relevance to current efforts to reform the public health system in SA and other LMICs where there is a focus on expanding access to mental health care [23–25]. To ensure that study findings are used to expand access to mental health counselling, we are planning to provide all participating clusters with training on the service integration model found to be most effective and cost-effective.

## Trial status

Enrolment of PHC clusters began on 19 April and individual participants began on 17 May 2017. Recruitment is ongoing and is expected to run through December 2018.

## Abbreviations

ART: Antiretroviral therapy
AUDIT: Alcohol Use Disorders Identification Test
CES-D: Center for Epidemiology Scale on Depression
CHW: Community health worker
CMD: Common mental disorder
HrQoL: Health-related quality of life
LMIC: Low- and middle-income country
MI: Motivational interviewing
NCD: Non-communicable disease
PHC: Primary health care
PST: Problem-solving therapy
QALY: Quality-adjusted life year
SAG: Stakeholder Advisory Group
TAU: Treatment as usual
WCDOH: Western Cape Department of Health
